### Blinding

Due to the physical differences between the treatment regimens, it is not possible to blind either participant or physician to the treatment. To address issues of blinding, wound photo documentation will be obtained during the trial and confirmation of wound closure will be assessed via blinded assessment of photos by independent observers, which will serve as the method of primary endpoint analysis.

### Setting

This multicenter study will be conducted in abdominal surgical hospital departments with the required manpower as well as structural and scientific qualifications. For both treatment arms, a maximum treatment time of 42 days to achieve complete wound closure shall be provided to cover 80% of participants, whether healing occurs by secondary or delayed primary closure [4]. All participants will be followed up for 90 days (three months) after the maximum treatment time, independent of whether a wound closure was achieved or not, or at which time point within the maximum timeframe for active treatment the wound closure was achieved. Thus, a general follow-up date for all study participants will be at Day 132. A follow-up period of three months after the active treatment period allows for an assessment of recurrence of the wound dehiscence or impairment as well as an adequate assessment of health economic relevant issues. Participants who have not achieved wound closure after 42 days will be seen at 45 days (six weeks) after the end of active treatment time (Day 87). This timeframe allows for a complete assessment of wound progression after study treatment and an assessment of wound closure that is achieved later than Day 42. Figure 1 gives an overview of the study flow. Study therapy will be started on participants in ambulatory care or in hospital and may be continued in ambulatory care. Due to the scope of the trial to evaluate outcomes and benefits of V.A.C.® Therapy when compared to SCWT when used across these care settings, all patients at the time point of randomization or inclusion, or during the active treatment period of 42 days that are eligible for outpatient care and have reasonable access to it, have to be transferred to outpatient care. The transfer of appropriate patients to outpatient care will be monitored and a missing transition that is not due to the medical condition of the patient or the need to provide the optimal treatment will be considered to be a protocol violation.

**Figure 1 F1:**
[figure not shown]
**SAWHI-study flow chart.** The figure shows the SAWHI overall study flow.

### Type of participants

#### **
*Diagnosis*
**

There are two categories of wound patients with distinct post-surgical open abdominal wound diagnoses that will qualify for this study. Patients with primarily closed post-surgical abdominal wounds without fascial dehiscence that develop a spontaneous wound dehiscence or require an active reopening of the wound by the treating physician may be included in the trial. Furthermore, patients with open post-surgical abdominal wounds without fascial dehiscence that cannot be closed by primary intention and require further treatment to achieve permanent closure are appropriate for trial participation.

### Inclusion and exclusion criteria

Only patients meeting all inclusion criteria and no exclusion criteria should be included in the study. No deviation will be granted for waiver of inclusion criteria and/or exclusion criteria. Table 1 gives an overview of the inclusion and exclusion criteria of the trial. Patients to be included in the SAWHI-study must have a post-surgical abdominal wound with intact fascia and be willing and able to provide written informed consent. At time of inclusion the minimum wound size must be eligible for both possible study treatment arms according to the therapeutic requirements of the respective randomized treatment arm. Inclusion, randomization, adequate wound pre-treatment (debridement) and start of therapy must be performed within 48 hours after reopening of the wound, diagnosis of non-closable wound or in case of spontaneous wound dehiscence.

**Table 1 T1:** SAWHI inclusion and exclusion criteria

**Inclusion criteria**	**Exclusion criteria**
Written informed consent	Age <18 years
Diagnosis of post-surgical subcutaneous abdominal wound healing impairment	Expected non-compliance with study procedures, visit schedule, and follow-up
Minimum wound size eligible for both possible study treatment arms	Pregnancy
Inclusion, randomization and start of therapy within 48 hours after initial diagnosis	Present or nonclosable defect of the abdominal fascia
	Any pre-existing or ongoing organ system failure, that cannot be stabilized or solved by appropriate medical treatment
	Necrotic tissue with eschar present
	Non-enteric and unexplored fistulas
	Malignancy of the wound
	Use of any other device based on the principle of negative pressure wound therapy on the study wound within ≤ 8 days prior to screening
	Competing therapy and procedures at the time of inclusion

The table shows the inclusion and exclusion criteria for SAWHI-study participants.

### Exclusion criteria

A patient unable or unwilling to comply with the protocol and study-related requirements, to sign the informed consent form, or to have their legally authorized representative act as a surrogate will be excluded from study participation. If a potential study patient, in the estimation of the clinical investigator, is unable to comply, the patient must be excluded from participation.

If the defect of the abdominal fascia is present at the time point of initial diagnosis or reopening of the wound, but can be closed before randomization but within the timeframe of 48 hours, participants may be included in the study. Any concomitant therapies or procedures deviating from the clinical standard wound treatment or with investigational character (for example, use of hyperbaric oxygen therapy) are not allowed ≤ 30 days prior to screening. The need for concomitant therapies or procedures that, in the opinion of the treating physician, would directly affect wound healing, or the ability to observe wound healing, is an exclusion criterion for trial participation. Concurrent participation in another trial that directly interferes with, or is likely to interfere in the foreseeable future with study procedures, patient’s compliance, wound healing or targeted endpoints is not allowed for participants of this trial.

### Intervention and comparison

This study is designed to evaluate treatment effects of a medical device in comparison to control therapy. Trial intervention is wound treatment with V.A.C.® using the basic principle of NPWT (Figure 2). The V.A.C.® therapy system is a non-invasive wound therapy system that uses controlled, localized negative (that is, subatmospheric) pressure to create an environment that promotes wound healing in chronic and acute wounds. The V.A.C.® therapy system label has been on the market since 1995 and bears the CE mark and includes the trade name and address of the manufacturer, the batch code, and all other essential information according to European Union (EU) Directive 1993/42/EEC. The V.A.C.® therapy system promotes wound healing through optimization of blood flow, decreasing local tissue edema, and removing excessive fluid from the wound bed. These physiologic changes facilitate the removal of bacteria from the wound. Additionally, the cyclical application of subatmospheric pressure alters the cytoskeleton of the cells in the wound bed through microstrain, triggering a cascade of intracellular signals that increases the rate of cell division and subsequent formation of granulation tissue. Moreover, this system has been shown to also cause macrostrain, bringing the edges of the wound closer and also stimulating wound bed granulation. [11] The V.A.C.® therapy devices that will be used in this study include the ActiV.A.C.® Therapy System, InfoV.A.C.® Therapy System, V.A.C. Freedom® ,V.A.C. Via® and V.A.C. Ulta® Therapy Systems. All V.A.C.® Therapy devices to be utilized in this study bear the CE mark and will be operated within normal conditions of use. In addition, all dressings to be used in the treatment group (V.A.C.® Therapy) bear the CE mark and will be used according to clinical guidelines. The use of the allocated V.A.C.® Therapy System should be performed according to the clinical guidelines released by KCI. Devices can be used with the black GranuFoam™ Dressing, V.A.C. GranuFoam Silver® Dressing, or V.A.C.® White Foam Dressing as indicated by the treating physician. Dressing changes are recommended to be performed every 48 to 72 hours, no fewer than three times per week, with frequency adjusted by the clinician as appropriate. Furthermore any concomitant therapies or procedures deviating from the clinical standard wound treatment or with investigational character (for example, use of hyperbaric oxygen therapy) are not allowed during the course of the trial.

**Figure 2 F2:**
[figure not shown]
**Vacuum Assisted Closure (V.A.C.®).** The figure shows the foam dressing fitted into the wound that helps to provide the necessary mechanisms to promote granulation tissue formation. The Sensa T.R.A.C.™ pad regulates pressure at the wound site and the V.A.C.® Therapy Unit provides intermittent and continuous therapy with integrated patient safety features. Copyright by KCI with permission for use for study related publications.

Incidents, complications or adverse reactions like pain during dressing changes, maceration, cellulitis or bleeding, and so on, have been reported only sporadically while using V.A.C.® therapy for treating acute and chronic wounds. Potential adverse events can usually be avoided or significantly reduced by complying with the basic rules of vacuum therapy (as detailed in the manufacturer’s instructions for use and guidelines for the use of V.A.C.® Therapy) as well as by the use of specifically designed vacuum device systems [32-34].

Control therapy is defined as any standard conventional wound therapy (SCWT) according to local clinical standards. Standard therapy is defined as the currently accepted and widely used treatment for the respective wound type, based on the results of past research. Therapy options for standard wound care are treatments that experts agree to be appropriate, accepted, and widely used. Health care providers are obligated to provide patients with best practice and standard of care.

### Type of analysis

The primary efficacy parameter, time to complete wound closure, will be compared between the two treatment groups using a log-rank test. In addition, as a supportive analysis, a Cox proportional hazards regression will also be used in order to assess if there is a difference between treatment groups while accounting for the effect of study center and wound size (appropriate baseline and medical history parameters will also be considered). The secondary efficacy parameter, incidence of complete wound closure, will be analyzed using a chi-squared test comparing the two treatment groups. As a supportive statistical analysis, logistic regression will also be implemented. The logistic regression will include treatment, study center, and wound size. Reduction in wound area (cm^2^) and wound volume (cm^3^) will be assessed using a three-factor (treatment group, study center, and time) analysis of covariance with baseline wound area (or volume) recorded at baseline to be used as a covariate. One planned interim analysis will be performed when 250 study participants have completed the first phase of the study. The interim analysis will validate the assumptions made for the study sample size calculation and will determine if sample size re-estimation is warranted.

The results of the SAWHI-V.A.C.®-study will be analyzed by the intention-to-treat (ITT) approach. The ITT analysis population will include all randomized participants who have a valid baseline and at least one valid post baseline wound assessment (examination). For the ITT analysis population, participants will be assigned to the treatment group based on the randomization schedule, regardless of the treatment actually received. For the analysis of the primary efficacy endpoint, missing values will be incorporated as censored values. For secondary endpoints, methods for imputing missing or partially missing data will be used as appropriate. The last observation carried forward (LOCF) method will be used for the analysis of the endpoints ‘incidence of wound closure’; ‘recurrence’ and ‘reduction of wound size’ in case of study determination or death.

As a secondary approach, a per protocol (PP) analysis will be performed without patients with any protocol deviations. Violations of inclusion and exclusion criteria; changes of randomized therapy; the use of concomitant therapies or procedures deviating from the clinical standard wound treatment or with investigational character (for example, use of hyperbaric oxygen therapy) and dressing changes not performed as recommended to be performed every 48 to 72 hours (no fewer than three times per week) will be considered as protocol deviations. Furthermore, during analysis, concomitant therapies or procedures will be evaluated regarding its impact to directly affect wound healing or the ability to observe wound healing.

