### Randomization

Randomization to treatment arms will be performed at a 1:1 ratio. Randomization will be performed via a centralized system with an Internet-based tool. Patients will be randomized dynamically. The permuted block sizes will randomly vary between 2, 4, and 6.

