### Stratification

Stratification will take place by study center and then also subsequently by wound size (cm^3^) within study center. Wound size categories or strata to be considered will be wounds ≤ 60 cm^3^ and wounds > 60 cm^3^.

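### Randomisation is stratified by centre and wound size, but the primary log-rank and the secondary chi-squared test ignore the strata; if the strata are prognostic, both tests are valid but conservative and less powerful than stratified ones

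*Protocol article*

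**What the plan says.** Protocol article, Stratification: "Stratification will take place by study center and then also subsequently by wound size", with two size categories split at 60 cm³. Under Randomization, allocation is 1:1 and "The permuted block sizes will randomly vary between 2, 4, and 6".

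Protocol article, Type of analysis: the primary parameter, time to complete closure, "will be compared between the two treatment groups using a log-rank test". The secondary parameter, incidence of closure, "will be analyzed using a chi-squared test comparing the two treatment groups". No stratum is mentioned for either test. A Cox model is added as supportive, "in order to assess if there is a difference between treatment groups while accounting for the effect of study center and wound size". A logistic model with treatment, centre and wound size is likewise supportive for incidence.

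Determination of sample size again names a plain log-rank test. It sizes the trial with an ordinary chi-squared test: 50% v 62.5% closure at 42 days, 80% power, 249 per group at α = 0.048.

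**The concern.** Blocking within centre and wound-size cells removes most of the chance imbalance between arms on those factors. An unstratified test still counts that imbalance in its variance. If the factors predict closure, the variance is too large for the design actually used. The test then rejects less often than its nominal level under the null, and less often than a stratified test under the alternative.

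Two things are at stake. One is power that the randomisation has already made available. The other is coherence: the deciding p-value comes from a test that ignores the design, while the model that respects it is only supportive. Near the 0.048 boundary the two could fall on opposite sides, with the less efficient one deciding.

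**Working it through.** **1. The plan's own figure.** Two-sided, pooled variance, no continuity correction:

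n per group = [z₁₋α/₂ √(2p̄q̄) + z₀.₈₀ √(p₀q₀ + p₁q₁)]² / (p₁ − p₀)²

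Here p₀ = 0.50, p₁ = 0.625 and p̄ = 0.5625, so the two roots are √0.4922 = 0.7016 and √0.4844 = 0.6960.

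- α = 0.05: (1.960 × 0.7016 + 0.8416 × 0.6960)² / 0.015625 = 246.1, rounded up to 247 (stated: 246).
- α = 0.048: the same with z = 1.977 gives 249.1, rounded up to 250 (stated: 249).

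Power at 249 per group is 80.0%. The stated size is reproduced, and it assumes no gain from stratification. With exponential times the implied hazard ratio is ln 0.375 / ln 0.5 = 1.415. With 249 × 1.125 ≈ 280 events, Schoenfeld's formula gives 82% power for the log-rank.

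**2. Assumptions not in the documents.** The article gives no closure rates by wound size or centre, and no number of centres. Assumed: two equal wound-size strata; exponential closure times; large wounds closing at 1/k the rate of small ones, k = 2, 3, 4; marginal closure held at 50% v 62.5%; 249 per arm; |z| > 1.977.

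**3. Hand check for the chi-squared test.** Let x be the share of large wounds still open at day 42 in the control arm. Then xᵏ is the share of small wounds, and 50% overall closure requires x + xᵏ = 1. Closure is x in small wounds and 1 − x in large ones. The between-stratum share of the variance 0.25 is r = (2x − 1)². With balanced strata the effective critical value is 1.977/√(1 − r).

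| k | x | r | effective critical value | actual type I error |
|---|---|---|---|---|
| 2 | 0.618 | 0.056 | 2.035 | 4.2% |
| 3 | 0.682 | 0.133 | 2.124 | 3.4% |
| 4 | 0.724 | 0.202 | 2.213 | 2.7% |

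For power, y + yᵏ = 0.75 gives the treated arm. With k = 2, y = 0.500, so treated closure is 75% (small) and 50% (large).

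- True SE of the difference: √[(0.2361 + 0.2188)/249] = 0.0427.
- Null SE of the chi-squared test: √(0.4922/249) = 0.0445.
- Null SE within strata: √(2 × 0.2313/249) = 0.0431.
- Power, chi-squared: Φ[(0.125 − 1.977 × 0.0445)/0.0427] ≈ 81%.
- Power, within strata: Φ[(0.125 − 1.977 × 0.0431)/0.0427] ≈ 82%.

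The same steps give 82% v 86% for k = 3 and 83% v 89% for k = 4.

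**4. Simulation of both tests**, blocks of 2, 4 and 6 within stratum:

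| Rate in large wounds | Log-rank type I error, unstratified | Log-rank power, unstratified v stratified | Power, chi-squared v Cochran-Mantel-Haenszel |
|---|---|---|---|
| 1/2 | 4.4% | 84% v 86% | 81% v 82% |
| 1/3 | 3.3% | 86% v 90% | 83% v 86% |
| 1/4 | 2.5% | 87% v 94% | 83% v 88% |

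Repeat runs moved the type I error by about 0.3 points and the power by one or two. With equal rates in both strata there is no gain (81% v 81%).

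**5. Adding centres.** Log-rank with N = 498, 10 to 40 centres, half of the wounds in each size stratum, and normal centre effects on the log hazard:

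| Centre SD, wound-size hazard ratio | Type I error, unstratified | Power, unstratified | Power, every centre × size cell | Power, size only |
|---|---|---|---|---|
| 0, 1 | about nominal | 0.81–0.83 | 0.76–0.82 | 0.81–0.83 |
| 0.3, 1.5 | 0.036–0.041 | 0.84 | 0.82–0.84 | 0.84–0.85 |
| 0.5, 2 | 0.031–0.033 | 0.85–0.86 | 0.88–0.90 | 0.88 |
| 0.8, 3 | 0.015–0.025 | 0.88–0.90 | 0.95–0.97 | 0.92–0.93 |

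Monte Carlo error is about 0.004 for type I error and 0.007 for power. Stratifying on every cell costs about 5 points (0.81 to 0.76) with 40 centres and non-prognostic strata. Size alone costs nothing there and secures part of the gain elsewhere.

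**The case against.** The strongest reply is that nothing planned is lost. The sample size rests on an unstratified chi-squared test at 80%. In every scenario examined the unstratified log-rank keeps at least 0.81 and the chi-squared about 0.79 or more. A simple primary test that matches the sample-size method, backed by prespecified adjusted models, is a defensible choice, and readers will get the adjusted estimates anyway. This stands, and it limits the point to efficiency and consistency.

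Second, the effect depends on prognostic strength, which the article does not quantify. This also stands. With weak strata the gain is negligible, and with none a fully crossed stratification can lose power. Against that, the design stratifies on both factors and adjusts for both, the endpoint is full epithelialisation within 42 days, and control care follows local standards. Some prognostic effect is therefore plausible.

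Third, the analysis plan is not shown and might stratify the tests. That carries less weight: the article names the tests and gives the models with centre and wound size a supportive role, which implies that the main tests leave these factors out.

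A reader might infer that the primary test is invalid or the trial underpowered. The documents support neither. The error is on the conservative side, and the 80% was computed for an unstratified test. Nor do they support saying without condition that the tests lose power, or that every centre should be crossed with wound size in the test.

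**Conclusion.** The mismatch between the stratified randomisation and the unstratified main tests is on the page. If the strata are prognostic, the log-rank and chi-squared tests run below their nominal 4.8% and give up power against stratified versions. Under two equal wound-size strata with a two- to fourfold difference in closure rate, the loss is about 2 to 7 points for the log-rank and 1 to 5 for the chi-squared test. With weak strata it is close to nil, and with non-prognostic strata it is nil. These sizes rest on assumed stratum shares, rates and exponential times, none of which the article gives. The change is worth making because it is cheap and lines the deciding test up with the design, not because the present test would mislead.

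**What to change.** Before unblinding, amend the analysis wording as follows:

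- Make the primary test a log-rank stratified at least by the 60 cm³ wound-size category.
- Include centre only after pooling small centres, for example by country, under a rule fixed before unblinding.
- Take the hazard ratio from the Cox model stratified in the same way, so that test and estimate agree.
- Replace the chi-squared test for incidence by a Cochran-Mantel-Haenszel test on the same strata.
- Keep the unstratified tests as sensitivity analyses.

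The cost is wording plus the pooling rule. No patients or data are added, and the sample size can stay as it is. The pooling rule is needed because sparse centre × size cells could cost up to about 5 points of power with many small centres if the strata turn out not to be prognostic. Stratifying by wound size alone avoids that risk, but it leaves some conservatism if centres differ.

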### Secondary clinical endpoints

The incidence of wound closure achieved within each treatment arm will be evaluated after a maximum study observation/treatment period of 42 days. These wound closures have to be confirmed as being sustained for a minimum of 14 subsequent days. This will be conducted via blinded photographic analysis. Recurrence of wound opening after initial closure and confirmed wound closure will be assessed and compared between the treatment groups. Reduction of wound size over time will be evaluated using reduction in wound volume and wound surface area over time.

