### SAWHI-website, photo documentation platform and verification of clinical wound size estimation

A study-website has been set up that contains all relevant information about the trial as well as a personal login area for each participating study center and a web-based photo documentation platform for wound photographs of study participants. The website can be found using the uniform resource locator http://www.sawhi.com. Wound photographs will be uploaded by study sites for each trial visit. The Wound Healing Analyzing Tool (WHAT) has been integrated within the platform. A centralized wound analysis of anonymized photographs (blinded assessment of wound photos) will be performed, which facilitates the objective evaluation of wound healing processes. Secondary endpoints (numerical parameters) like circumference (mm), area (mm^2^), maximum length (mm), and height (mm) will be calculated from the wound image using WHAT whereas the application of the system also will be performed by blinded independent assessors.

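### The wound-size ANCOVA lists time as a factor but names no within-participant term, so if fitted as written the treatment main effect is tested with too small a standard error; the fixed LOCF rule can add bias

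*Protocol article*

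**What the plan says.** Under Secondary clinical endpoints, the protocol article makes wound size a longitudinal outcome: "Reduction of wound size over time will be evaluated using reduction in wound volume and wound surface area over time". The section on the photo documentation platform confirms repeated data collection: "Wound photographs will be uploaded by study sites for each trial visit".

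Under Type of analysis, wound area and wound volume "will be assessed using a three-factor (treatment group, study center, and time) analysis of covariance". The model also adjusts for starting size, "with baseline wound area (or volume) recorded at baseline to be used as a covariate". Time stands in the same list as treatment and center. The sentence names no participant term, repeated-measures term or covariance structure. It does not say whether an interaction is included or which term carries the treatment comparison.

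The same section fixes a rule for missing values: "The last observation carried forward (LOCF) method will be used for the analysis of the endpoints" of closure incidence, recurrence and wound-size reduction, "in case of study determination or death" (the word before death is presumably meant as termination). For other gaps in secondary endpoints, "methods for imputing missing or partially missing data will be used as appropriate".

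**The concern.** Wound sizes from one participant at successive visits are correlated, also after adjustment for baseline size. A model with only treatment, center, time and baseline size has a single residual term, so it would count each visit as if it came from a new participant. The information about the treatment main effect would be overstated, and a nominal 5% test would reject too often when there is no effect.

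LOCF is a separate matter. Wounds are expected to shrink, so carrying forward the last value holds a departed participant's wound at an earlier and usually larger size. The estimated difference then depends in part on who left and when. In a model without a participant term, the carried-forward copies would also be counted as new data.

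At stake is the reported precision, and possibly the estimate, for two named secondary efficacy measures in a trial meant to meet the quality requirements of a reimbursement decision.

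**Working it through.** **The plan's own figures.** The article gives no number for the wound-size analysis. Its only sizing concerns closure rates of 50% versus 62.5% at 80% power. That reproduces closely with a two-sided chi-squared calculation: 247 per group against the stated 246 at α = 0.05, and 250 against 249 at α = 0.048. 498/0.9 gives 554 in total against the stated 550. Nothing below alters it.

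**Inputs.** Stated: 1:1 allocation, and 498 participants before allowance for loss. Not stated, so assumed: visits per participant m = 2 to 12; correlation between visits given baseline, ρ = 0.2 to 0.8; 25 centers for the simulation.

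**Treatment main effect, visits treated as independent.** With equal correlation between visits, the variance is understated by the design effect DE = 1 + (m − 1)ρ. The true standard error is √DE times the reported one. The actual two-sided error is 2 × [1 − Φ(1.96/√DE)].

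Example: m = 4, ρ = 0.5. DE = 1 + 3 × 0.5 = 2.5; √DE = 1.58; 1.96/1.58 = 1.24; error = 0.215.

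| m | ρ = 0.2 | ρ = 0.5 | ρ = 0.8 |
|---|---|---|---|
| 2 | 0.074 | 0.110 | 0.144 |
| 4 | 0.121 | 0.215 | 0.288 |
| 6 | 0.166 | 0.295 | 0.381 |
| 8 | 0.206 | 0.356 | 0.446 |
| 12 | 0.273 | 0.442 | 0.531 |

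Over this grid the true standard error is 1.10 to 3.13 times the reported one.

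**Simulation check** (498 participants, 25 centers, 6,000 replicates, no treatment effect, baseline-adjusted):

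| Setting | Visits as independent | Participant as unit |
|---|---|---|
| m = 4, ρ = 0.5 | 0.214 | 0.051 |
| m = 6, ρ = 0.3 | 0.215 | 0.048 |
| m = 6, ρ = 0.5 | 0.293 | 0.048 |
| m = 6, AR(1) 0.8 | 0.343 | 0.051 |

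**Treatment-by-time contrast.** Here the error runs the other way. A within-participant change has its variance reduced by the factor (1 − ρ), which the single-residual model ignores. The reported standard error is therefore 1/√(1 − ρ) times the true one: 1.12 at ρ = 0.2, 1.41 at 0.5 and 2.24 at 0.8. In the same four simulations, the last-versus-first-visit contrast had a type I error of 0.006 to 0.023.

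**LOCF, worked example.** Assumed: 50% of baseline size remains at day 21 and 20% at day 42, and those who leave do so at day 21. An arm with dropout d then shows 20(1 − d) + 50d = 20 + 30d percent at day 42.

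- No true effect, 10% dropout in both arms: 23% and 23%, so no false difference.
- No true effect, 5% control and 15% treated: 21.5% and 24.5%, a false difference of +3.0 points. Reversed: −3.0. Because the error is 30 times the gap in d, 0% versus 10% also gives 3.0 points.
- True difference of −10 points (treated arm 45% at day 21, 10% at day 42, hence 10 + 35d). Equal 10% dropout: 13.5 − 23 = −9.5. Control 5%, treated 15%: 15.25 − 21.5 = −6.25. Control 15%, treated 5%: 11.75 − 24.5 = −12.75.

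**The case against.** The strongest reply is that this is one sentence in a condensed journal article. A list of three factors is not a full model statement, and time in such a list is compatible with a repeated-measures ANCOVA whose error structure is set out in a full protocol or SAP that is not shown. Covariance structure and interactions are commonly left to those documents. This stands in part. A reader might infer that the plan declares visits independent or rules out a treatment-by-time term; the article says neither. What remains is that it commits to a specific model with a stated factor list, and that list alone does not suit repeated measurements.

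A reader might also infer that all confidence intervals for wound size would be too narrow. That is not supported. It holds for the treatment main effect; for treatment-by-time contrasts the test would be conservative. Since the article does not say which term is tested, the direction of the error in the reported result cannot be settled.

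The size of the error rests on visit numbers and correlations that the article does not give. At two visits and a correlation of 0.2, the inflation is modest (7%).

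On LOCF, equal dropout produces no false difference under the null, and the sizing section assumes at most 10% loss in both groups, so 15% in one arm exceeds that planning figure. A reader might infer that LOCF favors one particular arm; nothing in the article supports a direction. But a gap of 0% versus 10% stays within the planning figure and has the same effect, and LOCF is a stated rule, not a gap left to another document.

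**Conclusion.** The point holds conditionally for the model and directly for LOCF.

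If the ANCOVA is fitted with only the terms listed, inference on wound area and volume is invalid. For the treatment main effect, the true error of a nominal 5% test exceeds 5% everywhere in the assumed range, from about 7% to 53%; at ρ = 0.5 it is about 22%, 29% and 36% for 4, 6 and 8 visits. For treatment-by-time contrasts the standard error is too large. Whether the model will be fitted that way cannot be known from the article.

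LOCF biases the comparison when the amount or timing of dropout differs between arms, by about 3 points for a 10-point gap under the assumed healing course. It slightly dilutes a true effect when dropout is equal (−9.5 instead of −10). Its direction in this trial is unknown.

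Only secondary endpoints are touched. The primary log-rank analysis and the sample size are unaffected. The change is worth making, but the trial's main conclusion does not depend on it.

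**What to change.** State that time is a within-participant factor, and say which term gives the treatment comparison. Either of two analyses would serve:

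- a mixed model for repeated measures with treatment, visit, treatment-by-visit, center and baseline size, a specified within-participant covariance, and the day-42 treatment contrast as the main estimate; or
- a participant-level ANCOVA of day-42 wound size on treatment, center and baseline size.

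Replace LOCF for wound size by the likelihood-based mixed model, which uses all observed visits, or by multiple imputation (needed with the day-42 ANCOVA). State separately how deaths are handled: a mixed model left to itself implicitly estimates wound size after death, so dropping LOCF does not resolve that question. If a full protocol or SAP already treats time as a repeated factor, a clarifying sentence is enough for the model part, and only the LOCF rule needs changing.

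The cost is a short change of wording and standard software, with no extra data or participants. Intervals for the treatment effect will be wider than those from the model as written. The mixed model and standard multiple imputation rest on a missing-at-random assumption, which should be stated.
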